# **General information**

**Title registration at UMIN**: Evaluation of conjunctival hyperemia induced by Glanatec ophthalmic solution 0.4%

**UMIN Number**：UMIN000019565, date of registration; 30/10/2015

**Funder**: Kowa Company, Ltd. [name]

# **Project summary**

The purpose of this study is to investigate the onset, offset, and kinetic changes of conjunctival hyperemia induced by 0.4% ripasudil ophthalmic solution; Glanatec ophthalmic solution in participants with open-angle glaucoma or ocular hypertension (OHT). Ripasudil-naïve adults (n=50) with glaucoma who were undergoing eye drop treatment are enrolled. Slit lamp photographs and IOP measures are performed in one eye at baseline and 10, 60, 90, 120, 180 min after instillation of ripasudil. The resultant photographic images are objectively evaluated by 3 ophthalmic physicians using conjunctival hyperemia-analyzing software. Dependent variables are conjunctival hyperemia offset, clinical changes, IOP, and pixel coverage of conjunctival vessels post-instillation. We determine correlations between clinical grade and pixel coverage, and clinical grade and IOP reduction. In this clinical study, it is possible to clarify the onset, offset and kinetic changes of conjunctival hyperemia, induced by 0.4% ripasudil ophthalmic solution, in patients with open-angle glaucoma or OHT.

# **Rationale & background information**

Glaucoma can cause irreversible blindness, so numerous anti-glaucoma eye drops have been developed. Unfortunately, many patients with glaucoma still suffer from progressive visual defects and vision disorders. The most important risk factor for progression is intraocular pressure (IOP). Rho-associated protein kinase (ROCK) inhibitors lower IOP and are also associated with adverse events; most frequently, conjunctival hyperemia. In December 2014, ripasudil hydrochloride hydrate, a selective ROCK inhibitor (GLANATEC ophthalmic solution 0.4%) was launched as an anti-glaucoma treatment in Japan. A recent clinical trial with healthy participants investigated changes in conjunctival hyperemia and reduction of IOP within 2 h post-instillation of 0.4% ripasudil. Here, conjunctival hyperemia peaked 5-15 min post-instillation and resolved within 2 h. IOP values decreased between 30 min and 2 h post-instillation, regarding healthy participants. However, ripasudil-induced changes in conjunctival hyperemia over time have not been investigated in patients with glaucoma, who were previously treated with anti-glaucoma eye drops, other than ripasudil.

# **Study goals and objectives**

The primary endpoint of this study is to evaluate median offset time for conjunctival hyperemia induced by 0.4% ripasudil ophthalmic solution in patients with glaucoma. The evaluation is based on clinical grade scoring. The hyperemia offset time was determined as the time-point when clinical grade score increased by instillation of ripasudil returned to the baseline score. Additionally, the relationships among clinical grade changes over time, IOP, and pixel coverage on conjunctival blood vessels within 180 min post-instillation will also be evaluated for the secondary endpoints. The correlations between clinical grade and pixel coverage, and clinical grade and IOP reduction will be statistically analyzed. Furthermore, by using conjunctival hyperemia analyzing software, evaluation of conjunctival hyperemia will be more objective.

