# **Methodology Procedures**

Slit lamp photographs and IOP measures were performed between 12:00 and 14:00 before instillation as baseline and at 10, 60, 90, 120, 180 min after a single instillation ofripasudil. Binocular IOP values were compared and the eye with higher IOP value was selected at baseline. If the IOP value was the same in both eyes, the right eye was selected. The photographic method was held constant throughout this study, and the photographs were stored as JPEG images. In each participant, photographs of the bulbar conjunctiva on the temporal side were taken with a slit lamp (SL-D7; TOPCON, Tokyo, Japan). The angle between the slit lamp and the microscope arm was set at 30°. The camera flash light was adjusted to level one. The slit width was set 20 mm, and the objective magnification was set at 10. The diffuser of the slit lamp was used, and the resultant photographs were evaluated either by clinical grading or by automated hyperemia analysis software.

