**Clinical grade of conjunctival hyperemia**

Clinical grade of conjunctival hyperemia occurred at the temporal bulbar conjunctiva was evaluated in each case. The clinical grade scores were 0 (none: no hyperemia of the bulbar conjunctiva), 1 (mild: the dilation of a few conjunctival blood vessels), 2 (moderate: the dilation of some conjunctival blood vessels), and 3 (severe: the dilation of many conjunctival blood vessels), based on Japanese guidelines for allergic conjunctival disease.6 Clinical grades were evaluated by 3 medical ophthalmic physicians, using the photographs taken at each of the 6 time points. We selected the most frequent grade value generated by the 3 physicians. When the scores differed among the 3 physicians, we selected the maximum value.

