**Statistical analyses**

The statistical analyses were performed using the statistical package R, version3.4.1 (R Foundation for statistical Computing, Vienna, Austria). For the primary endpoint, median offset of conjunctival hyperemia, we used a (two-tailed) 95% confidence interval, as follows. The lower bound was the [(n+1)/2−
[figure not shown]
]-th value counted from the minimum value. The upper bound was the [(n+1)/2−
[figure not shown]
]-th value counted from the maximum value. (The value [(n+1)/2−
[figure not shown]
] was the whole number part of (n+1)/2−
[figure not shown]
.) Participants with no increases in clinical grade post-instillation, relative to baseline, are excluded from the primary endpoint. Secondary endpoints were assessed by using repeated-measure analysis of variance (ANOVA) for all 50 participants. Paired-*t* test was carried out when it was judged that there was a significant difference between the two groups using ANOVA. The data were expressed as means ± SDs. *P* values *****< 0.05 and ****<** 0.01 were considered statistically significant. The correlation between the clinical grade and the value of pixel coverage of the blood vessels, and clinical grade and IOP, were subjected to statistical analyses using the Jonckheere-Terpstra Trend Test.

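### The primary offset time can only be a visit time but is analysed as an exact time, so the median runs late and its 95% CI can miss the true median almost every time

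*Protocol*

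**What the plan says.** Under Study goals and objectives the protocol states: "The primary endpoint of this study is to evaluate median offset time for conjunctival hyperemia induced by 0.4% ripasudil ophthalmic solution". The same section fixes the definition: "The hyperemia offset time was determined as the time-point when clinical grade score increased by instillation of ripasudil returned to the baseline score".

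Methodology Procedures sets the assessments before instillation and "at 10, 60, 90, 120, 180 min after a single instillation". The section on clinical grade confirms that grades come only from these photographs: "using the photographs taken at each of the 6 time points". The Follow-Up section provides for none.

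Statistical analyses fixes the interval estimate: "For the primary endpoint, median offset of conjunctival hyperemia, we used a (two-tailed) 95% confidence interval". The lower bound is the "th value counted from the minimum value" and the upper bound the "th value counted from the maximum value", both at a rank of (n+1)/2 minus a term lost from the text as a figure. Eyes whose grade never rises are left out. No section treats the recorded times as interval-censored, or says what value an eye still raised at 180 min receives.

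**The concern.** Recovery is not observed when it happens. An eye raised at 60 min and back to baseline at 90 min recovered somewhere between the two, yet it enters the ranking as 90. Every such error points the same way, so it does not average out and more participants do not reduce it.

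The order-statistic interval knows nothing of this error. If both ranks fall on the same visit, the interval has zero width, for example 90 to 90 min, although the data place recovery only between 60 and 90 min. An eye unrecovered at 180 min has no observed value to rank at all.

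The trial tests no hypothesis, so this estimate and its CI are the whole primary result. As planned, they would overstate how long the hyperemia lasts and claim a precision the visit schedule cannot give.

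**Working it through.** **Inputs from the protocol.** Visits at 10, 60, 90, 120 and 180 min; target n = 50, fewer once eyes without a rise are dropped; two-sided 95% CI from order statistics.

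**Assumptions.** The missing term is the standard 1.96·√n/2. Each eye recovers once and stays recovered. True offset times are lognormal; their spread is not in the document, so log-SD is varied. 45 of 50 eyes are evaluable.

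**1. The rank formula with exact times.** k = integer part of (n+1)/2 − 1.96·√n/2, upper rank n+1−k, coverage = 1 − 2·P(Bin(n, 0.5) ≤ k−1).
- n = 50: 25.5 − 6.93 = 18.57, so ranks 18 and 33, coverage 96.7%.
- n = 45: 23 − 6.57 = 16.43, so ranks 16 and 30, coverage 96.4%.

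The formula is sound for exactly observed times.

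**2. What follows with no distribution.** An included eye must show a rise at 10 min or later, so the earliest recorded offset is 60 min. The recorded time can be late by up to 50 min (gap 10–60), 30 min (60–90), 30 min (90–120) or 60 min (120–180). If the true median is between 10 and 60 min, the lower limit cannot fall below 60, and coverage is 0% for any spread and any n.

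**3. Coverage with recorded times.** Let the true median M lie between two visits and let a be the earlier one. The CI covers M only if the lower limit is at a or before and the upper limit is after a. With p = P(T ≤ a) = Φ(ln(a/M)/σ), coverage = P(k ≤ Bin(n, p) ≤ n−k).

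Example, n = 45, M = 75, σ = 0.4: p = Φ(ln(60/75)/0.4) = Φ(−0.558) = 0.2885. Coverage = P(16 ≤ Bin(45, 0.2885) ≤ 29) = 20.2%.

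| True median (min) | Recorded median | σ = 0.3 | σ = 0.4 | σ = 0.6 |
|---|---|---|---|---|
| 45 or 55 | 60 | 0% | 0% | 0% |
| 65 | 90 | 75% | 85% | 92% |
| 75 | 90 | 4% | 20% | 55% |
| 85 | 90 | <0.1% | 0.7% | 17% |
| 95 | 120 | 87% | 91% | 94% |
| 110 | 120 | 8% | 29% | 63% |
| 150 | 180 | 4% | 20% | 55% |

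With n = 50 and M = 75, coverage runs from 0.0% at σ = 0.15 through 16.8% at 0.4 to 71.7% at 0.8. A median exactly on the 60- or 90-min visit is covered 98.4% of the time.

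**4. Zero width and censoring** (n = 45, σ = 0.4). At M = 75 about 45% of simulated CIs are 90 to 90 min. The upper limit is the 16th value from the top, so it falls on an unrecovered eye when at least 16 of 45 are still raised at 180 min. At M = 150, P(T ≤ 180) = 0.676 and this happens in 38% of trials. At M = 110 it practically never happens.

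**5. Remedies.** Taking the lower rank from left endpoints and the upper rank from right endpoints gave simulated coverage of at least 99.5% in the scenarios run. A lognormal interval-censored fit (n = 50, σ = 0.4) returned medians of 75.2, 85.0, 104.5 and 150.4 for truths of 75, 85, 105 and 150. It is weak when most recoveries fall between 10 and 60 min: a truth of 35 came back as 51.

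**The case against.** The best reply concerns what is being estimated. The protocol uses the same term, time point, for the scheduled photographs, so offset could mean the scheduled visit at which recovery is seen. For that discrete quantity the order-statistic interval is valid, and 90 to 90 min is a legitimate result. This is correct as far as it goes. But the protocol never states that reading; it names an offset time, and its stated aim is to describe the onset and offset of the side effect. If the visit-based quantity is meant, the definition and the reported result must say so.

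Other points stand in part. The spread, the number of evaluable eyes and the rank term are assumed, and undercoverage is not universal, as the table shows. Censoring at 180 min affects the interval only if recovery is slow; the background section reports resolution within 2 h in healthy participants. No analysis can locate a median inside the 10–60 min gap, and the endpoint-based CI is conservative. The trial is exploratory, and the error runs in the cautious direction for a side effect.

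None of this rescues the planned CI as a 95% interval for the offset time. Nor is it detail left to an analysis plan: the protocol itself fixes both the definition and the CI method.

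**Conclusion.** The concern holds and should be corrected before the primary result is reported. That the recorded median is never early, and that coverage is 0% for a true median between 10 and 60 min, follows from the visit schedule, given one lasting recovery per eye. The other figures depend on the stated assumptions: with 45 eyes and log-SD 0.3 to 0.6, a true median of 75 min is reported as 90 min with coverage of 4% to 55% instead of 95%. Coverage is worst for a median late in a gap with a modest spread, and near nominal at a visit or, with a wide spread, just after one.

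**What to change.** In the endpoint definition, record each offset as the interval from the last visit above baseline to the first visit back at baseline, or as beyond 180 min if recovery is not seen. In Statistical analyses, keep the ranks but apply the lower one to the sorted left endpoints and the upper one to the sorted right endpoints, with unrecovered eyes ranked last. Word the median as a bracket, for example between 60 and 90 min. This is the safest option because it assumes no distribution.

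A Turnbull estimate, or a lognormal or Weibull interval-censored fit with a likelihood or bootstrap CI, can be added. The parametric fit should not be relied on if most recoveries fall between 10 and 60 min.

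The cost is revised wording and a few lines of R. No new visits, participants or data are needed. The reported interval becomes wider.

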# **Study Design**

**Study design:** Multicenter, prospective, interventional, non-randomized open-label study.

**Trial characteristic:** Exploratory

**Purpose of intervention:** Treatment

**Type of intervention: Medicine:** At the beginning of trial, one drop of 0.4% ripasudil solution will be instilled to the subjective eye.

**Target sample size:** 50

This clinical trial was not based on a statistical hypothesis test, and 50 cases were taken as the target number of cases from the feasibility of this trial.

**Inclusion criteria:**

1. The participants were (males or females) over 20 years old with open angle glaucoma or OHT, poorly controlled by ophthalmic solutions and requiring additional treatment
2. Prior treatment with one or more of prostaglandin (PG) analogs, and/or beta-blockers, and /or acetazolamide
3. No history of treatment with ripasudil ophthalmic solution

**Exclusion criteria:**

1. Participants with hypersensitivity against ripasudil hydrochloride hydrate, anhydrous dihydrogen phosphate sodium, glycerin, sodium hydroxide, or concentrated benzalconium chloride liquid
2. Less than -12dB of mean deviation (MD) value
3. Women of childbearing potential who were pregnant, nursing, or planning a pregnancy
4. Secondary glaucoma (excluding exfoliation glaucoma)
5. Angle closure glaucoma
6. Refract value: Less than -9.0D, More than +9.0D
7. Participants whose intra ocular pressure cannot be measured by the iCare Tonometer
8. Participants with traumatic injuries
9. Participants with ocular inflammation of the anterior segment
10. Participants who cannot tolerate photo slit
11. Participants having with histories of surgeries during the past 6 months
12. Users of contact lenses
13. Individuals deemed unsuitable for this trial by doctors

# **Methodology Procedures**

Slit lamp photographs and IOP measures were performed between 12:00 and 14:00 before instillation as baseline and at 10, 60, 90, 120, 180 min after a single instillation ofripasudil. Binocular IOP values were compared and the eye with higher IOP value was selected at baseline. If the IOP value was the same in both eyes, the right eye was selected. The photographic method was held constant throughout this study, and the photographs were stored as JPEG images. In each participant, photographs of the bulbar conjunctiva on the temporal side were taken with a slit lamp (SL-D7; TOPCON, Tokyo, Japan). The angle between the slit lamp and the microscope arm was set at 30°. The camera flash light was adjusted to level one. The slit width was set 20 mm, and the objective magnification was set at 10. The diffuser of the slit lamp was used, and the resultant photographs were evaluated either by clinical grading or by automated hyperemia analysis software.

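### The reading that picks the higher-IOP eye also appears to serve as its baseline, so part of the secondary IOP reduction is regression to the mean

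*Protocol*

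**What the plan says.** All places are in the protocol.

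- **Eye selection (Methodology Procedures):** "Binocular IOP values were compared and the eye with higher IOP value was selected at baseline". Ties are settled by side: "If the IOP value was the same in both eyes, the right eye was selected". Selection therefore rests on the measured values.
- **Baseline (same section):** "Slit lamp photographs and IOP measures were performed between 12:00 and 14:00 before instillation as baseline". No screening reading, repeat reading or averaging is described.
- **Follow-up (Project summary):** "Slit lamp photographs and IOP measures are performed in one eye at baseline and 10, 60, 90, 120, 180 min after instillation of ripasudil". Only the selected eye is followed.
- **Design (Study Design):** "Multicenter, prospective, interventional, non-randomized open-label study". There is no comparison arm.
- **Role of IOP (Study goals and objectives):** IOP within 180 minutes is a secondary endpoint, and "The correlations between clinical grade and pixel coverage, and clinical grade and IOP reduction will be statistically analyzed". The primary endpoint is hyperemia offset time by clinical grade.
- **Analysis (Statistical analyses):** "Secondary endpoints were assessed by using repeated-measure analysis of variance (ANOVA) for all 50 participants". Paired t tests follow if the ANOVA is significant, and thresholds of 0.05 and 0.01 are set.

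**The concern.** Choosing the eye with the higher IOP is a reasonable rule. The difficulty is that the same reading then seems to be reused as the comparator.

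A reading is the eye's underlying pressure plus an error or short-term fluctuation. Picking the larger of two readings favours the eye whose error happened to be positive at that moment. The five later readings of that eye carry no such selection, so on average they lie below the baseline even if the drop does nothing. A fellow-eye series or a control arm would show how much of the fall comes from this, but the design has neither.

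At stake is the size of the secondary IOP reduction, which would be overstated, and the meaning of its p values.

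**Working it through.** The protocol states no IOP standard deviation, effect size or power, and its 50 participants were set by feasibility. There is no figure of its own to reproduce, so the artefact is computed under stated assumptions.

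**Inputs**
- From the protocol: n = 50; six time points (baseline and 10, 60, 90, 120 and 180 min); higher-eye rule; repeated-measures ANOVA, then paired t tests; significance at 0.05.
- Assumed: s, the SD of the error in one reading, 1 to 2 mmHg; d, the SD of the true difference between a participant's two eyes, 1 to 2 mmHg.

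**Step 1. Mean artefact, all error independent between eyes and over time.** The measured difference between the eyes has SD √(d² + 2s²). The expected error in the selected eye is

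false fall = [s² / √(d² + 2s²)] × √(2/π), with √(2/π) = 0.798.

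- d = 2, s = 1: 1/√6 × 0.798 = 0.33 mmHg
- d = 1.5, s = 1.5: 2.25/√6.75 × 0.798 = 0.69 mmHg
- d = 1, s = 2: 4/√9 × 0.798 = 1.06 mmHg

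Simulation agrees with the formula to within about 0.01 mmHg. Widening the assumptions to s from 1 to 2.5 and d from 0 to 3 mmHg gives 0.24 to 1.41 mmHg.

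**Step 2. Part of the error persists.** An eye-specific deviation that lasts through the 180 minutes does not regress. If half the error variance persists, the false fall is halved: 0.33/2 ≈ 0.16 mmHg at d = 2, s = 1, and 1.06/2 = 0.53 mmHg at d = 1, s = 2.

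**Step 3. Chance of a significant result with an inert drop.** Trials of 50 participants with six time points were simulated. A given post-dose versus baseline comparison counted only if the ANOVA was significant at 0.05 and the paired t test was too.

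| d, s (mmHg) | False fall (mmHg) | Significant, all error independent |
|---|---|---|
| 2, 1 | 0.33 | about 23% |
| 1.5, 1.5 | 0.69 | about 51% |
| 1, 2 | 1.06 | about 72% |

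With half the error variance persistent, the range is about 10% to 32%. These rates carry simulation error of a percentage point or two. Without the ANOVA step the paired t test alone gives higher rates (about 38% at d = 2, s = 1 and 80% at d = 1, s = 2), but that is not the procedure the protocol describes.

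**Step 4. Separate baseline reading.** With s = 1.5, d = 2 and an inert drop, using an independent second pre-dose reading of the chosen eye as baseline gives a mean false fall of 0.00 mmHg, and the paired t test alone rejects in 4.8% of trials. Under the protocol's rule the same assumptions give 0.62 mmHg and 57%.

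**The case against.** Several objections have force.

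- **The size has no anchor in the protocol.** This stands. Error common to both eyes cancels in the selection, and error that persists does not regress; both shrink the artefact. The direction holds as long as some eye-specific error does not persist, but the amount is a range under assumptions.
- **The comparator is inferred.** The Statistical analyses section does not name baseline as the reference for the paired t tests. This also stands, although baseline is the natural reference for a reduction and only one pre-instillation reading is described.
- **The trial is exploratory, IOP is secondary, and an inert drop is hypothetical.** True. The background section reports IOP falls in healthy participants, so the practical harm is an overstated reduction rather than an invented one. The protocol still sets significance thresholds, so the IOP result will be read inferentially.
- **A SAP could deal with it.** Only in part: without a second pre-dose reading or fellow-eye data, modelling cannot separate the artefact without outside assumptions about variability.

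A reader might also infer two further harms that the protocol does not support. One is a distorted relation between clinical grade and IOP reduction. The eye is not chosen on hyperemia, so in this model the false fall does not depend on grade and is the same at all five post-dose times; no grade trend follows among those readings. The other is a false early onset of IOP lowering. The onset the protocol sets out to study is that of hyperemia, and it defines no IOP-onset endpoint.

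**Conclusion.** The point holds for the size of the secondary IOP reduction. Under the protocol as written, the selecting reading appears to be the baseline, nothing in the design removes the resulting bias, and the reduction is overstated to some degree.

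With s and d each assumed to be 1 to 2 mmHg, the overstatement is about 0.3 to 1.1 mmHg if all reading error is independent, and about 0.16 to 0.53 mmHg if half its variance persists. The corresponding chance that a given comparison is significant with an inert drop is about 23% to 72%, or 10% to 32%. Confidence is high for the direction and limited for the magnitude.

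It would go too far to conclude that the whole IOP fall is artefact; only part of it is. Nor is the main result compromised. The protocol states: "The primary endpoint of this study is to evaluate median offset time for conjunctival hyperemia induced by 0.4% ripasudil ophthalmic solution in patients with glaucoma". That endpoint is based on clinical grade, and the eye is chosen on IOP.

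**What to change.** Keep the higher-eye rule. After the eye has been chosen, take a second IOP reading of that eye before instillation, and use only this second reading as baseline in the ANOVA, the paired t tests and the calculation of IOP reduction. Name it as the comparator in the Statistical analyses section. This removes the bias from error that is independent between the two pre-dose readings. A fluctuation still present at the second reading but fading later would leave a remainder.

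The cost is one sentence in the protocol, one more rebound-tonometer reading per participant (seconds, without anesthesia) and a somewhat smaller reported IOP reduction. Selecting the eye on an earlier clinic reading would also work in principle, but the protocol mentions no such reading for both eyes, so it cannot be assumed to exist.

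If the data are already collected, state in the report that the fall from baseline includes regression to the mean from eye selection, and do not attribute all of it to the drop.
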